### **2.3 Incidence of fatal and non-fatal cancer (excluding non-melanoma skin cancer)**

Morbidity and mortality from all-incident cancers (excluding non-melanoma skin cancers) will constitute a secondary endpoint. ASPREE cancers require histopathological confirmation unless metastasis is present on imaging or there is strong clinical evidence of metastasis. Mandatory reporting of all new cancers to state-based tumour registries in Australia, along with multiple mechanisms which are in place to ensure this data is complete (including routine surveillance of hospital discharge records and death certificates) will ensure robust cancer incidence data. In Australian and U.S. aged populations colon cancer will be a predominant incident cancer, being the second-leading cause of cancer related death. Because a common presentation of colon cancer is with rectal bleeding it is possible that the use of aspirin may cause ascertainment bias. However, this has not been documented in any of the intervention studies to date. In particular in the Nurses' Health Study the investigators controlled for use of screening endoscopy in all of the multivariate analyses. They also evaluated the influence of aspirin among women who did not report having a positive fecal occult blood test result or did not undergo screening endoscopy. Among such women, the influence of aspirin was not materially altered.

### **2.4 Dementia**

Assessment as described above in 1.2 and in flow chart (Figure 1, Appendix 1).

### **2.5 Mild cognitive impairment**

To assess the presence of Mild cognitive impairment (MCI) the routine visit battery of cognitive function tests (3MS, SDMT, Hopkins, COWAT) will be utilized. Figure 2, Appendix 1 illustrates the steps in assessment for MCI. Participants who have normal 3MS scores but whose Hopkins delayed recall and/or SDMT and/or COWAT test scores fall by more than 1 SD from their own baseline value will be provisionally categorized as having MCI. Normative data for the Hopkins will be obtained from the Hopkins VLT-R Manual, for the SDMT from the SDMT Manual (Western Psychological Services, 1982) followed by conversion from scaled scores, and for the COWAT from Kozora and Cullum^136. The advantages of using within-subject decline rather than a pre-specified cut-off of 1.5 SD below age-adjusted mean are that i) about 7% of the population function below 1.5 SD anyway, leading to a reduction in specificity, ii) decline is more indicative of likely (further) progression to dementia than a single cross-sectional low score, and iii) decline-based criteria can detect individuals with a progressive course before they fall below a defined cut-off of -1.5 SD (e.g.). For sub-classification of MCI, a decline in Hopkins delayed recall would be indicative of MCI-a (amnesic), a decline in either or both of the other tests indicates MCI-non-a (non-amnesic) and a decline in Hopkins delayed recall plus either of the

other tests indicates MCI-mixed.

In addition, those individuals who are triggered by a drop in 3MS score of  $> 10$  (adjusted for education level attained) or a score of  $< 78$  to undergo dementia assessment (see section 1.2), but who are not subsequently classified as having dementia based on DSM-IV criteria, will be provisionally categorized as having MCI. Even without a diagnosis of dementia, a decrease in 3MS score of  $\geq 10$  points is a measure of clinically significant cognitive decline. Assignment to MCI subcategories in these participants will be made by the endpoint adjudication committee on the basis of results from the routine cognitive exam and the triggered assessment. If no individual tests (other than the 3MS) have declined sufficiently to enable sub-categorization, the default category will be MCI-mixed.

[figure not shown]

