### 520 **5.4 Endpoint Ascertainment**

521 At each annual visit and 6 month telephone contact, the participant will be questioned as to the  
522 occurrence of any of the study endpoints over the previous 6 months. Notification of a potential  
523 study endpoint will trigger the collection of information for endpoint confirmation and adjudication  
524 by the EAC. All such events will be recorded in source documents and in the appropriate  
525 section of the Case Report Form (CRF). Confirmation of endpoints will be ascertained by  
526 collecting and forwarding information from the following sources within 90 days of learning the  
527 event:

- 528 • Details from medical records from the usual treating physician or practice-held medical  
529 record.

- Medical records obtained by letter/fax/email contact with other treating specialist physicians or secondary/tertiary medical care centers.
- CRFs containing standardized questionnaires for the assessment of cognitive function, physical function and quality of life.
- In Australia, hospital records/discharge summaries, pathology reports, Medicare and Pharmaceutical Benefits Scheme (PBS) records.
- Death Certification: In both Australia and the U.S., the respective National Death Index will be routinely sourced for notification of death not identified through the above processes.
- For dementia endpoint ascertainment, the Dementia Adjudication Panel will be responsible for providing the assessment according to DSM-IV criteria. An individual's 3MS score below 78, or fall over time by more than 10 points adjusted for age and level of education, will trigger additional and uniformly applied cognitive and functional testing by research staff and the collection of ancillary data (laboratory tests and a CT or MRI) for endpoint ascertainment.
- For significant disability as a primary endpoint, the loss of one of the Katz Activities of Daily Living will be defined as self or proxy report of having 'a lot of difficulty with' or 'unable to perform' one or more ADLs at the annual follow-up contact. For all deaths where disability data is missing in the year preceding death, we will conduct a proxy interview to determine whether there was disability in the year prior to death and its approximate onset. We will also conduct a follow-up phone call to determine the persistence of the reported disability by repeating the same interview items.

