### **6.2 Exclusion criteria**

- A history of a diagnosed cardiovascular event defined as MI, congestive heart failure, angina pectoris ( $\pm$  nitrate use), stroke, transient ischemic attack,  $>50\%$  carotid stenosis or previous carotid endarterectomy or stenting, coronary artery angioplasty or stenting, coronary artery bypass grafting, or abdominal aortic aneurysm.
- A clinical diagnosis of atrial fibrillation.
- A serious intercurrent illness likely to cause death within the next 5 years, such as terminal cancer or obstructive airways disease.
- A current or recurrent condition with a high risk of major bleeding, e.g. cerebral aneurysm or cerebral AV malformation, any bleeding diathesis, gastrointestinal malignancy, recent peptic ulcer, liver disease, esophageal varicosities, uremia, aortic aneurysm or any other condition known to be associated with a high risk of serious bleeding.
- Anemia, i.e. hemoglobin level below the normal value for the gender of the participant (males:  $<12$  g/dL, females:  $<11$  g/dL)

(Note: Hemoglobin levels within the normal range in a participant taking therapy for anemia will not be an exclusion criterion).

- Absolute contraindication or allergy to aspirin.
- Current participation in a clinical trial.
- Current continuous use of aspirin for secondary prevention.
- Current continuous use of other anti-platelet drug or anticoagulant.
- A systolic blood pressure  $\geq 180$  mmHg and / or a diastolic blood pressure  $\geq 105$  mmHg
- A history of dementia or a Modified Mini-Mental State Examination (3MS) score  $\leq 77$  as measured at Visit 1: *Lifestyle Profile and Screening*.
- Severe difficulty or an inability to perform any one of the 6 Katz ADLs, as determined at Visit 1: *Lifestyle Profile and Screening*.
- Pill-taking compliance below 80% during the placebo run-in phase.

People with previous or current use of aspirin for reasons other than secondary prevention may enter the trial, provided they agree to cease existing use of aspirin and understand that they may be subsequently randomly allocated to low dose aspirin or placebo. In the case where a person has been advised by their doctor to take aspirin, the person should seek advice from their doctor before participating in the study.

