Appendix 1. Figure 2.  
Flowchart for Mild Cognitive Impairment assessment to reach a secondary endpoint.  
MCI-a (amnesic); MCI-non-a (non-amnesic)

In all cases, the provisional diagnosis of MCI will require confirmation of the decline (i.e. relevant result(s) still  $> 1$  SD below baseline, or 3MS still  $> 10$  (adjusted) points below baseline, or still  $< 78$ ) at reassessment at 12 months. For those showing a decline indicative of MCI only at the last assessment, reassessment confirming the decline will be required 3 months later. (The 1 year timing allows reassessment to occur at the time of a scheduled routine visit, reducing assessment costs. The 3 month interval for those declining only at the final assessment avoids delaying analysis and publication unnecessarily.)

MCI, as traditionally defined by a deficit of  $-1.5$  SD in a cognitive domain or domains in the presence of preserved general cognition (3MS  $> 77$ ), is not a study entry exclusion criterion. While those subjects ultimately destined to decline to dementia will be picked up at subsequent

2167 assessments on the decline criteria used in ASPREE for MCI, a planned sub-group analysis will  
2168 also be performed on the MCI category and sub-categories, after exclusion of any falling below -  
2169 1.5 SD on the relevant measure on entry.

2170 We wish to emphasize that MCI is a secondary endpoint and that one of ASPREE's strengths is  
2171 that its test battery will allow several alternatives to identifying and defining MCI that may be  
2172 useful for future large trials in this population.

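### MCI cases found on the 3MS alone default to MCI-mixed, a subtype that the same section defines by decline on at least two other tests

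*Protocol*

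**What the plan says.** All of this is in Appendix 1, section 2.5, unless stated otherwise.

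- **Test-based route.** Participants with a normal 3MS whose Hopkins delayed recall, SDMT or COWAT falls by more than 1 SD from their own baseline are provisionally MCI. A fall in Hopkins delayed recall alone gives the amnesic subtype, and a fall in SDMT or COWAT alone the non-amnesic one. The mixed subtype is "a decline in Hopkins delayed recall plus either of the" other two tests.
- **3MS route.** Those sent for dementia assessment because the 3MS dropped by more than 10 points or is under 78, but "who are not subsequently classified as having dementia based on DSM-IV criteria, will be provisionally categorized as having MCI". The adjudication committee assigns the subtype from the routine and the triggered tests. When that yields nothing: "If no individual tests (other than the 3MS) have declined sufficiently to enable sub-categorization, the default category will be MCI-mixed".
- **Confirmation** (text under Figure 2 of Appendix 1). "In all cases, the provisional diagnosis of MCI will require confirmation of the decline". On the 3MS route this means either still more than 10 points below baseline or still under 78, at 12 months (3 months for a decline first seen at the last assessment).
- **Entry** (section 6.2). Excluded are "A history of dementia or a Modified Mini-Mental State Examination (3MS) score" of 77 or less. The lowest eligible baseline is therefore 78.
- **Benchmark and rationale.** Section 2.5 treats a 3MS fall of 10 points or more as clinically significant. It prefers decline to a cut-off because decline is more "indicative of likely (further) progression to dementia than a single cross-sectional low score".

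**The concern.** The main problem is the default label. Sub-category results for MCI are planned, and a reader of those results will take MCI-mixed to mean memory plus another domain. Under the default it also contains people in whom no domain test moved. They are probably closer to unclassified than to multi-domain impairment.

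The secondary problem is the fixed cut-off, which sits exactly at the entry threshold. The step described as confirming a decline can be met by a second low score with almost no change from baseline. If test noise in people who entered near 78 produces such events, they weaken the contrast between the arms for this secondary endpoint.

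**Working it through.** **1. The two subtype rules side by side.**

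| Rule | Hopkins delayed recall | SDMT or COWAT |
|---|---|---|
| Definition of MCI-mixed | must decline | at least one must decline |
| Default to MCI-mixed | no sufficient decline | no sufficient decline |

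A defaulted case meets neither half of the definition. The default applies after the committee has looked, so committee review does not remove the conflict.

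**2. Smallest fall that satisfies the 3MS route.** For baseline b, a score of 77 is enough, which is a fall of b − 77. The alternative is a drop of more than 10, so 11 points. The smallest qualifying fall is min(b − 77, 11).

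| Baseline | 78 | 79 | 80 | 82 | 85 | 86 | 87 | 88 and above |
|---|---|---|---|---|---|---|---|---|
| Smallest fall | 1 | 2 | 3 | 5 | 8 | 9 | 10 | 11 |

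The fall is below 10 whenever b − 77 < 10, that is for baselines 78 to 86. The protocol varies between a drop of more than 10 and of 10 or more. Under the second reading, 88 and above becomes 10 and nothing else changes.

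**3. How often noise alone could do this.** The protocol gives no 3MS distribution and no measurement error, so everything in this step is assumption. For a stable true score T and error SD s, the chance of an integer score under 78 is p = Φ((77.5 − T)/s). Two independent scores under 78 have chance p².

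- T = 78: s = 2 gives p = 0.401, p² = 0.161; s = 5 gives p = 0.460, p² = 0.212.
- T = 80: s = 2 gives p = 0.106, p² = 0.011; s = 5 gives p = 0.309, p² = 0.095.

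A simulation extends this to a whole cohort: normal true scores, no true decline, rounded scores, entry at 78 or above and three test-and-retest pairs. Noise-only MCI events per 19,000:

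| Assumed true mean / SD | Within-person SD | Below-78 arm | More-than-10-point arm |
|---|---|---|---|
| 92 / 6 | 2 | about 68 | about 0 |
| 92 / 6 | 4 | about 162 | about 185 |
| 90 / 7 | 2 | about 227 | about 0 |
| 90 / 7 | 4 | about 460 | about 225 |
| 94 / 4.5 | 2 to 4 | about 3 to 13 | about 0 to 139 |

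The below-78 arm therefore ranges from a handful to about 460. Which arm is noisier depends on the assumed error and distribution.

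**4. Is the 3MS route likely to be used?** Appendix 1, section 1.2 cites a positive predictive value for dementia of about 0.33 for scores under 78. If that carried over to this trial, about 1 − 0.33 = 0.67 of such triggers would not be dementia and would become provisional MCI.

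**The case against.** **On the label.** The default is an openly stated fallback, it does not change who counts as MCI, and the committee may draw on the triggered assessment (ADAS-cog, figure-ground task, Color Trails) before using it. All of that is true. It means that not every case without a Hopkins, SDMT or COWAT decline will be defaulted, and the share of MCI-mixed affected is unknown. It does not reconcile the default with the definition.

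**On the cut-off.** The 1-point route is written explicitly as a persistent-low-score arm. It needs a dementia assessment at least 6 weeks after the trigger, a decision that the participant is not demented, and a second low score. A CES-D 10 score of 8 or more can add referral and retesting. The decline rationale is written about people with normal 3MS scores and a −1.5 SD cut-off. A reader might infer that the 1-point route contradicts a formal definition of MCI. It does not: it is in tension only with the section's rationale and its 10-point benchmark. None of the extra steps, however, sets a minimum fall.

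**On safeguards.** The planned sub-group analysis drops participants below −1.5 SD on the relevant measure at entry. If that measure were the 3MS, the limit would be 92 − 1.5 × 6 = 83 or 90 − 1.5 × 7 = 79.5 under two of the assumed distributions, and most low entrants would leave. The protocol does not say whether the 3MS is meant, and the analysis is additional: it changes neither the endpoint nor the label.

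**On stakes.** Appendix 2 puts the main interest under MCI in the rate of change of the 3MS, which neither rule touches. This stands and keeps the point modest. The MCI flowchart is not shown, so a further condition there cannot be ruled out.

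**Conclusion.** The subtype conflict is established from the text alone: the default places people with no domain decline in the subtype that requires at least two. It affects the sub-category results, not total MCI. A reader might infer that subtype results become unreadable. The protocol does not support that, because the number of defaulted cases is unknown.

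The missing minimum fall is also established (baselines 78 to 86, down to 1 point from 78), but it is a design choice with a trade-off, not an error. A reader might infer hundreds of false events. That figure rests wholly on assumed score distributions, and equally admissible assumptions give about 3. Some of those events would also be people whose true score is under the cut-off and who were over-scored at entry. With blinded 1:1 allocation, both issues dilute a treatment effect or blur the subtypes; they do not favour an arm.

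**What to change.** 1. In Appendix 1, section 2.5, replace the MCI-mixed default with a separate category, for example *MCI, 3MS only/unspecified*. Count it in total MCI and keep it out of the amnesic, non-amnesic and mixed subtypes. Align the MCI flowchart.
2. Keep the below-78 arm in the stated endpoint. Add a sensitivity analysis of MCI that requires the protocol's own within-person decline, confirmed at reassessment: either the 3MS change criterion, or a fall of more than 1 SD on Hopkins delayed recall, SDMT or COWAT.
3. Report how many MCI events rest on the below-78 arm alone, by baseline 3MS, so that the size is read from data and not from assumptions.

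The cost is wording and a small change to the classification algorithm. No new data are needed. The MCI-mixed group will be smaller, and the sensitivity analysis will have somewhat fewer events than the main one.

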Appendix 1. Figure 2.  
Flowchart for Mild Cognitive Impairment assessment to reach a secondary endpoint.  
MCI-a (amnesic); MCI-non-a (non-amnesic)

In all cases, the provisional diagnosis of MCI will require confirmation of the decline (i.e. relevant result(s) still  $> 1$  SD below baseline, or 3MS still  $> 10$  (adjusted) points below baseline, or still  $< 78$ ) at reassessment at 12 months. For those showing a decline indicative of MCI only at the last assessment, reassessment confirming the decline will be required 3 months later. (The 1 year timing allows reassessment to occur at the time of a scheduled routine visit, reducing assessment costs. The 3 month interval for those declining only at the final assessment avoids delaying analysis and publication unnecessarily.)

MCI, as traditionally defined by a deficit of  $-1.5$  SD in a cognitive domain or domains in the presence of preserved general cognition (3MS  $> 77$ ), is not a study entry exclusion criterion. While those subjects ultimately destined to decline to dementia will be picked up at subsequent

2167 assessments on the decline criteria used in ASPREE for MCI, a planned sub-group analysis will  
2168 also be performed on the MCI category and sub-categories, after exclusion of any falling below -  
2169 1.5 SD on the relevant measure on entry.

2170 We wish to emphasize that MCI is a secondary endpoint and that one of ASPREE's strengths is  
2171 that its test battery will allow several alternatives to identifying and defining MCI that may be  
2172 useful for future large trials in this population.

## 2173 **2.6 Physical ADL disability**

2174 A secondary endpoint will be reached with a loss, confirmed at 6 months, of ability to perform  
2175 one Katz ADL (as described above in section 1.3.).

## 2176 **2.7 Depression**

2177 A modified 10 questions version of the CES-D will be used. The modification omits questions  
2178 related to lifestyle that are covered by the LIFE questionnaire. A score of 8 or higher on the 30  
2179 point CES-D 10 questions version is deemed clinically significant and a secondary endpoint  
2180 will have been reached.

2181 Any such score will be communicated back to the family physician, and would typically result in a  
2182 clinical assessment.

2183 Anyone discharged from hospital with a principal diagnosis of depression will be deemed also to  
2184 have reached a secondary endpoint for depression.

## 2185 **2.8 Major hemorrhagic events - Clinically significant bleeding**

2186 Gastrointestinal hemorrhages or hemorrhages at other sites that required transfusion,  
2187 hospitalization, prolonged hospitalization, surgery, or are fatal will be considered as clinically  
2188 significant bleeding events. Source information from clinical case notes and hospital medical  
2189 records related to these events will be collected and sent to the ASPREE Data Management  
2190 Center. A clinically significant bleed may lead to temporary or permanent trial medication  
2191 cessation, according to the treating physician or surgeon's clinical judgment, but not exit from  
2192 the trial. There is no standard accepted clinical trial definition of major GIT bleed in Australia.  
2193 Our operating definition has been accepted by the Australian Gut Foundation.

## 2194 **3. Other Measures:**

### 2195 **3.1 Cognitive function**

2196 In addition to the 3MS, the following depression and cognitive function tests will be administered  
2197 at baseline and biennially, unless otherwise specified.

2198 **a) Depression** - The CES-D 10 is administered in conjunction with the 3MS to ensure that a low  
2199 score on the 3MS is not the result of depression. It will also be administered annually to  
2200 ascertain new onset depression.

2201 It is judged impractical to rely on clinical assessments of depression being sufficiently  
2202 standardized across sites, countries and types of practice (family physicians *versus*  
2203 psychiatrists) to enable substitution of clinical assessments for CES-D 10 scores.

2204 In the context of a participant's 3MS score declining to the dementia assessment trigger  
2205 range (as described in section 1.2), any participant also scoring 8 or more on the CES-D 10  
2206 will be referred to their usual physician for assessment and treatment, and will then be  
2207 reassessed in ~3 months. If the CES-D 10 score has returned to below 8, or if the CES-D 10  
2208 was 8 or higher at baseline, but the 3MS score (adjusted according to Tombaugh) is still in  
2209 the trigger range, we will proceed with the additional dementia assessment as usual. If the

adjusted 3MS has returned to above the trigger, the participant continues in the study without going through the dementia assessment. If the CES-D 10 remains at or >8, their usual physician is advised for further management of the patient.

We will perform exploratory bivariate analyses to measure the association between performance on individual cognitive tests and depression. Depression in early Alzheimer's Disease has been found not to increase in severity, indicating that progressive cognitive changes sufficient to diagnose dementia are unlikely to be confounded by depression.

**b) SDMT-** An additional non-language based test of cognitive function, the Symbol-Digit Modalities Test (SDMT), is also included in cognitive function assessment as a measure of executive function, specifically of processing speed and activation, as well as of complex visual scanning. The SDMT has been used longitudinally in other large-scale studies (e.g.,) and has been shown to be sensitive to both age-related cognitive decline and the increasing load of cerebrovascular disease. The SDMT does not use the alphabet. It is therefore not likely to penalize illiterate or semi-literate individuals, or those educated in languages not using the English alphabet. It is also easy to administer and score, and has both high 'ceiling' and low 'floor' effects, making it useful in assessment across a wide range of abilities.

**c) Hopkins Verbal Learning Test- Revised (HVLTR) -** The HVLTR^79 is a test of immediate and delayed recall, and delayed recognition. It has been widely used in previous studies of cognitive impairment. It is sensitive to change, has validated age and education-adjusted norms, and takes less time to administer than other word lists frequently used to test memory (such as the Rey Auditory Verbal Learning Test or the California Verbal Learning Test).

**d) Controlled Oral Word Association Test (COWAT) -** The COWAT is a measure of executive function and verbal fluency. Patients are asked to generate as many words as possible beginning with the letter F. This is a shortened version of the full COWAT, which uses FAS, CFL, or PRW. Normative data for individual letters is available for this age group (e.g.), and there has been shown to be high internal consistency between F, A and S, and C, F, and L, with coefficient alphas of 0.83 in each case. It should also be noted that a measure of verbal fluency by semantic category is included within the 3MS.

